**Methods:**

This is a single-centered, partially randomized, placebo-controlled, double-blind feasibility trial. One hundred pregnant women with a history of depression and/or anxiety/PDA will be recruited and randomized into one of four arms, which could include the following: receiving a daily dose of both investigational products and dietary counseling on increasing dietary fiber, receiving a daily dose of both investigational drugs only, receiving fish oil investigational product and placebo, and a control arm with no intervention. The study involves six study visits, all of which can be conducted virtually every 3 months from the time of enrollment. At all study visits, information on diet, mental health, physical activity, and sleep quality will be collected. Additionally, all participants will provide a stool sample at each visit.

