## Methods

### Trial design and setting

This is a single-centered, partially randomized placebo-controlled double-blind feasibility trial with three intervention arms (Gutopia, Gutboost, and Gutless) and one active control. In total, 100 pregnant women with a history of depression and/or anxiety/PDA attending Sunnybrook Hospital Clinics in the Greater Toronto Area will be recruited.

Participants in Gutopia will receive a daily dose of both investigational products and dietary counseling on increasing dietary fiber. Participants in Gutboost will receive a daily dose of both investigational supplements, while participants in the Gutless arm will receive fish oil and a placebo. Participants in Gutless and Gutboost will be blinded to the status of the placebo/probiotic they will be receiving. The study member interacting with the patients will also be blinded to the treatment group the participant is assigned to. Participants who fully consent to receiving both investigational products, including placebo, will be fully randomized to one of the intervention arms. Participants not willing or able to take a placebo or probiotics will be assigned (not randomized) to the appropriate group that accommodates their preferences/needs. Participants unable or unwilling to take any of our investigational products will be assigned to the active control arm. Women in the control arm will receive standard care offered to all obstetric patients seen at the hospital.

The study involves six study visits, all of which can be conducted virtually every 3 months from the time of enrollment (**Figure 1**). The last study visit will happen between 9 and 12 months postpartum. Two of the study visits will occur during pregnancy [enrollment (visit 1) and third trimester (visit 2)], with the remaining occurring at 1, 3, 6, and 9 months postpartum. At all study visits, information on diet, mental health, physical activity, and sleep quality will be collected. Additionally, all participants will provide a stool sample at each visit, using our stool collection kits, which will be shipped to or dropped off at our center.

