#### Exclusion criteria

Prepregnancy BMI > 30.Low income (unable to afford basic daily needs).Single parents without any kind of family support.Having a child with significant mental/physical disability.Previously diagnosed with other major mental health disorders.Taking prescription medications (other than SSRIs/SNRIs/TCA).Smoking and recreational drug use.Dietary restrictions or allergies to fish oils.Repeated antibiotic use.Women are unable to switch to study brand supplements.Multiparous women with young children (i.e., one or more children less than 4 years of age at the time of delivery).No/low English reading comprehension.

Our inclusion criteria allow for antidepressant/anxiety use. Medication use is an important prognostic factor that can significantly alter mental health outcomes. Hence, the number of patients treated with an antidepressant/anxiolytic needs to be equally distributed among all arms. To achieve this, we will use stratified randomization using two strata (treated vs. untreated) through a computer-generated process using permuted blocks of three and six. The process will be repeated separately for untreated participants.

Preexisting and diagnosed major mental health disorders will be determined at the time of screening using a modified version of the Mini International Neuropsychiatric Interview (MINI). The MINI, conducted by a trained research team member, will allow for confirmation of a history of anxiety/depression and an absence of current anxiety/depression and other major mental health disorders (bipolar, schizophrenia, psychosis, etc.).

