#### Statistical analysis

Should the trial succeed and we continue to recruit for a larger trial, the following statistical plan will be used to compare mental health outcomes between the groups: we will use mental health scores as the primary outcome and an intent-to-treat approach for these analyses.

Participants lost to follow-up will be assumed to have lost interest/commitment to the study and will be excluded from the analysis. Those who discontinue treatment will still be included.

Between-group differences for EPDS/GAD-7 scores will be analyzed using analysis of covariance (ANCOVA), with group membership as the independent variable, EPDS/GAD-7 as dependent, and pharmacotherapy, exercise status, and any form of psychotherapy as covariates.

The interaction effect between the O3FA and probiotics model will be analyzed and reported in each model. Alternative models will be used if the assumptions of ANCOVA are violated. If differences are found between groups, appropriate *post-hoc* analyses will be conducted to identify where the differences lie. Within-group differences at each time point will be analyzed using repeated measures ANOVA. Data from each follow-up will be compared to baseline scores. EPDS/GAD-7 scores will be the dependent variables, and follow-up times will be our independent variable.

Each stool sample will undergo shotgun metagenomics for taxonomic and functional output readings. A comprehensive analysis of all findings will be conducted by an experienced bioinformatics expert at Zymo Research. All researchers involved in the stool analysis will be blinded to the type of intervention. The relationship between each intervention and the relationship to EPDS and GAD-7 scores will be analyzed and reported by an experienced bioinformatician.

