## Discussion

Given the prevalence of PDA and its resulting impact on quality of life and infant well-being, the importance of investigating underutilized and overlooked nonpharmacological options is paramount. Specifically, the need to investigate alternative approaches in comparison to prescription medication and psychotherapy has been identified as an important need by expecting and new mothers. It is anticipated that pregnant women with a history of depression and anxiety will be particularly interested in partaking in this trial, resulting in favorable recruitment rates. Given the positive findings of O3FA and probiotic supplements on mental health symptoms in nonpregnant adults, we expect a similar trend in PDA symptoms, with a low likelihood of adverse events.

While not our main objective, we anticipate a correlation between the microbial composition and probiotics and O3FA supplementation. As several recent studies have demonstrated a positive impact of probiotics (19–21) or O3FAs (22, 23) on mental health outcomes via changes in the gut microbiome, this has yet to be demonstrated in individuals at risk of PDA. Having intervention groups that provide both supplements (Gutboost) versus O3FA alone (Gutless) will allow us to determine potential interaction between these supplements. We anticipate a difference in mental health scores between the Gutboost and Gutless intervention groups. Incorporating a third intervention arm where dietary counseling is provided in addition to supplementation (Gutopia) further allows us to understand the interaction between diet and supplementation. We anticipate differences in mental health scores between Gutopia compared to the other intervention arms. Additionally, having an active control arm can potentially inform the magnitude and directionality of these changes by comparing outcomes in the intervention arms (*N* = 75) to the active control arm (*N* = 25).

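### Only three arms are randomised and control is filled by assignment, yet the planned EPDS/GAD-7 comparisons do not separate randomised from assigned women

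*Protocol article*

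**What the plan says.** **Allocation.** Under Trial design and setting the study is a "partially randomized placebo-controlled double-blind feasibility trial with three intervention arms (Gutopia, Gutboost, and Gutless) and one active control". Randomisation is open only to women who consent to both products and to placebo, and its destinations are the intervention arms. For others: "Participants not willing or able to take a placebo or probiotics will be assigned (not randomized) to the appropriate group that accommodates their preferences/needs". Women who are unable or unwilling to take any product go to control. The abstract (Methods) puts it differently: "One hundred pregnant women with a history of depression and/or anxiety/PDA will be recruited and randomized into one of four arms".

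**Balance.** The text under Exclusion criteria says that "the number of patients treated with an antidepressant/anxiolytic needs to be equally distributed among all arms". It relies on randomisation stratified by treated versus untreated, in permuted blocks of three and six.

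**Blinding.** "Participants in Gutless and Gutboost will be blinded to the status of the placebo/probiotic they will be receiving". No participant blinding is described for Gutopia or control.

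**Analysis.** The Mental health outcome section plans between-group comparisons of EPDS and GAD-7 scores. For a continued trial, Statistical analysis sets out an intent-to-treat ANCOVA "with group membership as the independent variable", adjusted for pharmacotherapy, exercise and psychotherapy. The Discussion says that setting the intervention arms (75 women) against control (25 women) "can potentially inform the magnitude and directionality of these changes".

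**The concern.** Willingness or ability to take a supplement or a placebo may go with prior supplement use, expectations and prognosis, and EPDS and GAD-7 are self-reported. Where arm depends on that willingness, a difference in scores between arms can reflect who was placed there and not what they took.

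The analysis text refers only to group. It does not say which women reached the group by randomisation. A reader of the abstract would take all four-arm contrasts as randomised and blinded. All three intervention arms receive fish oil, so control is the only arm without study omega-3. Any conclusion about fish oil itself therefore rests on the non-randomised comparison.

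**Working it through.** **1. Entry routes, from Trial design and setting.**

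| Arm | Randomised entry | Entry by assignment | Participant blind |
|---|---|---|---|
| Gutopia | Yes | Possible, number not given | None: she receives dietary counselling |
| Gutboost | Yes | Possible, number not given | Holds if randomised; not if placed there because she declines placebo |
| Gutless | Yes | Possible, number not given | Holds if randomised; not if placed there because she cannot or will not take the probiotic |
| Control | None | All | None |

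Criteria for study withdrawal adds a later, also non-random, route into control: women withdrawn from the intervention for side effects may continue there. That has to be reconciled with the intent-to-treat statement.

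**2. Block sizes.** Blocks of 3 and 6 divide evenly by three arms (remainders 0 and 0) but not by four (remainders 3 and 2). This agrees with a three-arm randomisation and contradicts the abstract. Stratified blocks can balance medication only among the women they allocate, so not in control and not among assigned women.

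**3. Plan's own figures.** 75 + 25 = 100, which agrees with the stated total. The sample size has no power inputs, so nothing further can be reproduced. An equal split of the 75 would give 75 / 3 = 25 per intervention arm; the article does not state this. The number randomised is 75 minus the women assigned to intervention arms, a figure that is not given.

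**4. Illustration on assumed values.** The document gives no prognostic difference and no share of assigned women, so both are assumed here. Take no true effect, a two-sided test at 0.05 and no covariate adjustment. With selection bias b in SD units,

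se = sqrt(1/n1 + 1/n2), and rejection rate = P(|Z + b/se| > 1.96).

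*Control versus intervention.* Every control is assigned, so b is the full shift in prognosis. At 25 versus 75, se = sqrt(1/25 + 1/75) = 0.231.

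| Assumed shift (SD) | Rejection, 25 vs 75 | Rejection, assumed 100 vs 300 |
|---|---|---|
| 0.2 | 0.139 | 0.41 |
| 0.3 | 0.255 | 0.74 |
| 0.5 | 0.581 | 0.99 |

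*Gutboost versus Gutless.* If a share f of one arm is assigned and those women differ by d SD, b = f × d. For f = 10% to 40% and d = 0.2 to 0.5, b runs from 0.1 × 0.2 = 0.02 to 0.4 × 0.5 = 0.20 SD. At 25 per arm (se = sqrt(2/25) = 0.283) rejection is 0.051 to 0.109. At an assumed 100 per arm it is 0.052 to 0.293.

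On these assumptions the control comparison is the serious problem. The contrast within the intervention arms is only mildly affected at this trial's size and becomes more exposed if recruitment continues.

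**The case against.** The strongest reply is that the design is disclosed. The abstract and the design section both say partially randomised, the assignment rule is stated openly, and the recruitment section gives its reason: to respect preferences in a pragmatic study. This stands. A reader might infer that the protocol presents itself as a fully randomised trial; it does not. What remains is the abstract's four-arm clause, the balance statement for all arms and the unqualified double-blind label.

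Second, the trial is about feasibility. Outcomes measured makes process evaluation primary and the mental health data exploratory, and the ANCOVA applies only if recruitment continues. This stands too, and limits the reach of the point. However, the between-group comparisons under Mental health outcome carry no such condition. Microbiome profiling also speaks of continuing enrolment if the trial succeeds, so these women may enter the later analysis.

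Third, pooling is inferred: the model text is silent on assignment route, and an SAP could define a randomised-only set. That is fair, but the analysis as written draws no such line.

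Fourth, a reader might conclude that Gutboost versus Gutless is certainly contaminated, or put a bias in EPDS points on it. The document does not support that. Women who decline placebo could all go to Gutopia. The recruitment section can also be read as sending anyone who cannot take either supplement to control. Nor can controls be described as all having refused, since inability is also a route. Lastly, medication imbalance is not ignored: pharmacotherapy is a planned covariate.

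**Conclusion.** The point holds for the comparative EPDS/GAD-7 analyses and for three descriptive statements. Control has no randomised entry, which contradicts the four-arm wording in the abstract. Stratified randomisation cannot balance medication in an arm it does not fill. Participant blinding is secure only for women randomised to Gutboost or Gutless. Analysed by group as written, intervention arms may mix randomised and assigned women, and the 75 versus 25 comparison is observational throughout.

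The primary feasibility outcomes are not touched. The size of any bias is unknown: the rejection rates shown depend on assumed shifts and shares and only indicate sensitivity. A valid randomised comparison among the three intervention arms remains available from the randomised women; none is available against control.

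**What to change.** 1. Record each woman's assignment route (randomised, or assigned and why) in the trial database from the start.
2. Make the main comparative EPDS/GAD-7 analysis randomised women only, by allocated arm, keeping the planned adjustment for pharmacotherapy, which is also the stratification factor. Identify Gutboost versus Gutless as the only contrast that is both randomised and participant-blinded.
3. Report women assigned to intervention arms separately. A pooled analysis may be kept as a sensitivity analysis.
4. Label every comparison with control as observational, including the 75 versus 25 comparison in the Discussion.
5. Correct the abstract to randomisation among three arms with control by assignment, and limit the balance and double-blind statements to the randomised women and arms to which they apply.

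The preference design itself can stay. The cost is one data field, some rewording and a smaller comparative set; how much smaller depends on the number assigned, which the article does not give.

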### Randomization and baseline evaluation

All eligible patients interested in participating will be consented to and randomized or assigned to an intervention or control arm based on responses during screening. If eligible for full randomization, this will be completed by the study principal investigator using a computer-generated randomization via random permuted blocks. The study coordinator will only be informed of the status of randomization to the Gutopia arm and will be blinded to the Gutboost and Gutless arms.

Once randomized, the participant will be scheduled for the baseline assessment as soon as possible. If scheduled as a virtual visit, a stool kit will be mailed to the participant or provided at their prenatal visit. There is no predetermined time between the screening and baseline; however, the baseline visit will take place prior to the 35th gestational week (visit 2). The collection of baseline questionnaires will include the following: The Generalized Anxiety Disorder-7 (GAD-7), The Edinburgh Postnatal Depression Scale (EPDS), Single-Item Sleep Quality Scale, Pregnancy Physical Activity Questionnaire Consumer Financial Protection Bureau—Financial Wellbeing (CFPB-FWB), Demographic Questionnaire, and the Dietary Screening Form. Please see the supplementary materials for a breakdown of the versions used and the psychometric properties of each questionnaire. The baseline visit will also include the provision of a stool sample.

There will be a total of six study visits; visit 1 (baseline) and visit 2 will occur during pregnancy, with the remaining four scheduled to take place in the postpartum period (**Figure 1**). All questionnaires completed at baseline, with the exception of the CFBP-FWB, the Demographic Questionnaire, and the Dietary Screening Form, will be completed at all postpartum visits. A postdelivery questionnaire will be completed at visit 3 (~ 4–6 weeks postpartum), and a postpartum questionnaire will be completed at visits 4–6. The sessions will be 45–60 minutes in length.

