### The intervention

Participants in all intervention groups will receive a 200-ml bottle of Genestra brand Super EFA Forte Liquid Omega-3 Fatty Acid. Participants will be instructed to take 1 teaspoon a day with a meal.

Participants in the Gutopia and Gutboost intervention groups will receive HMF Maternity Probiotic Formula, a Genestra brand. Participants will be asked to take one tablet daily with food.

Details of both supplements are provided under Investigational products in the following section.

Only participants in Gutopia will receive a dietary intervention. Intervention is geared toward increasing gut-friendly foods via a flexible dietary plan aimed at increasing daily uptake of prebiotic and probiotic foods. A registered dietitian will use baseline food questionnaire data provided by each subject at enrollment to devise strategies and recommendations for increasing intake of pre/probiotic foods. The target goal is to include at least 35 g/day of fiber and at least one to two servings of fermented foods daily. The dietary intervention will also include recommendations minimizing highly processed foods high in sugar and fat. To improve adherence and accountability, weekly follow-ups by phone, virtual meeting, or email will be conducted by a trained study team member until patients have reached a level of confidence in attaining goals. During each follow-up, the study team will monitor the level of adherence to the study RD’s recommendations. These follow-ups will be designed to provide encouragement while helping patients address and prevent triggers that jeopardize their fiber intake.

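### Women who decline only the placebo are taken out of randomisation although two placebo-free arms fit them, which leaves the diet contrast (Gutopia versus Gutboost) partly non-randomised

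*Protocol article*

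**What the plan says.** All references are to the protocol article.

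- **Who is randomised** (Trial design and setting): "Participants who fully consent to receiving both investigational products, including placebo, will be fully randomized to one of the intervention arms".
- **Who is not** (same section): "Participants not willing or able to take a placebo or probiotics will be assigned (not randomized) to the appropriate group that accommodates their preferences/needs". Women who will take none of the products go to the control arm.
- **How assignment is made** (Randomization and baseline evaluation): eligible women are "randomized or assigned to an intervention or control arm based on responses during screening". The article gives no further rule.
- **What the arms contain** (Trial design and setting): Gutopia combines fish oil, probiotic and counselling on fibre intake. For the other two arms the section states: "Participants in Gutboost will receive a daily dose of both investigational supplements, while participants in the Gutless arm will receive fish oil and a placebo". The intervention section confirms that "Participants in the Gutopia and Gutboost intervention groups will receive HMF Maternity Probiotic Formula" and that "Only participants in Gutopia will receive a dietary intervention".
- **What the contrast is for** (Discussion): the Gutopia arm "further allows us to understand the interaction between diet and supplementation", and mental health scores are expected to differ between Gutopia and the other intervention arms.
- **Analysis** (Statistical analysis): for the larger continuation trial, ANCOVA of EPDS and GAD-7 by group membership, with pharmacotherapy, exercise and psychotherapy as covariates. No term distinguishes assigned from randomised women.

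**The concern.** The assignment rule treats every partial refusal alike, as if each left a single suitable arm. That is true of a woman who declines probiotics, but not of one who declines only the placebo, because two arms contain none.

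Gutopia versus Gutboost is the only pair of arms that isolates diet; Gutopia versus Gutless also differs by probiotic. If placebo-decliners enter these two arms by something other than chance and are analysed by group, the diet contrast mixes randomised and non-randomised women. They also bypass the stratified randomisation on which the Exclusion criteria section relies to spread antidepressant and anxiolytic users equally over the arms.

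Any who enter Gutboost raise a second problem. They know that they take the active probiotic, yet they would count in Gutboost versus Gutless, the comparison in which participants are meant to be blinded to probiotic or placebo.

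The Microbiome profiling section says that enrolment will continue into an efficacy trial if feasibility is shown, so the rule could carry forward.

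**Working it through.** **Step 1. Which arms fit each woman, from the arm definitions**

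| Woman's position | Arms that fit | Allocation in the article |
|---|---|---|
| Accepts both products and placebo | Gutopia, Gutboost, Gutless | Randomised |
| Declines placebo only | Gutopia, Gutboost | Assigned |
| Declines probiotic only | Gutless | Assigned |
| Declines all products | Control | Assigned |

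The second row is the only non-randomised group with more than one fitting arm.

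**Step 2. Inputs for the size**

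The Discussion gives 75 intervention women and 25 controls. Permuted blocks of three and six (Exclusion criteria section) are consistent with 1:1:1, so 75/3 = 25 per arm. The share *f* of the 75 who decline only placebo is not given; 10%, 20% and 30% are assumed, with 2% to show the low end. It is also assumed that none of the 75 declines probiotics. N = 100 rests on pilot-trial practice, so there is no power figure to reproduce.

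**Step 3. Randomised women per arm, Gutopia versus Gutboost**

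- Current rule: n = 75(1 − f)/3
- Decliners randomised 1:1 between the two arms: n = 75(1 − f)/3 + 75f/2
- Standard error of a standardised difference: √(2/n). With 1:1 allocation in both strata and a common SD, stratifying by placebo willingness leaves this formula unchanged.

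| f | Decliners | n per arm now | n per arm with change | SE now | SE with change | Fall in SE |
|---|---|---|---|---|---|---|
| 2% | 1.5 | 24.5 | 25.25 | 0.286 | 0.281 | 1.5% |
| 10% | 7.5 | 22.5 | 26.25 | 0.298 | 0.276 | 7% |
| 20% | 15 | 20 | 27.5 | 0.316 | 0.270 | 15% |
| 30% | 22.5 | 17.5 | 28.75 | 0.338 | 0.264 | 22% |

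This compares randomised women with randomised women. Pooling assigned women under the current rule would also raise n, but at the price shown in step 4.

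**Step 4. Possible shift if assigned women are pooled**

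Assume f = 20% (15 decliners, 20 randomised women per arm) and that decliners differ in mood score by 0.3–0.5 SD.

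- Split 80:20 towards Gutopia: 12 and 3 decliners, so arms of 32 and 23. Decliner shares are 12/32 = 0.375 and 3/23 = 0.130, a difference of 0.245. Shift = 0.245 × 0.3 to 0.245 × 0.5 = 0.07 to 0.12 SD.
- All to Gutopia: shares are 15/35 = 0.429 and 0. Shift = 0.13 to 0.21 SD.

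The split and the prognostic difference are both assumptions. An even split gives no shift from decliner status as such, and analysing randomised women alone removes the shift altogether.

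**The case against.** **Blinding may leave only Gutopia suitable.** Participants are blinded between Gutboost and Gutless, and the coordinator is told only who is in Gutopia. A known placebo-decliner cannot be blinded in Gutboost, so the fitting group might in practice be Gutopia alone. The article does not say so. If that were the rule, every decliner would sit in one arm of the diet contrast and the imbalance would be at its largest (step 4).

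**The change is not free.** This stands. If decliners now go to Gutopia, randomising them puts women into Gutboost who know they take probiotic. They have to be kept out of Gutboost versus Gutless. A reader might think that nothing is lost because such women are unblinded under assignment anyway, but that holds only for those now assigned to Gutboost, and the article names no arm.

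**Preference is a declared design feature.** The trial is described openly as partially randomised, and the recruitment section justifies this as inclusive and pragmatic, so there is no internal contradiction. But the refusals named in the rule concern placebo and probiotics, not diet. Randomising between two placebo-free arms respects them.

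**The trial is about feasibility.** Process evaluation is primary, and the mental health and microbiome data are exploratory or belong to the continuation trial. This stands and limits the weight of the point. Nor does the rule spoil the count of women randomised: how many accept full randomisation is itself useful information.

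**The article is condensed.** Figure 1 is not shown, and the full protocol may state where decliners go. It may therefore supply the missing arm, but an arm fixed by rule would still not be randomised.

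**Conclusion.** The point holds as a design weakness that should be corrected, with its effect confined to secondary contrasts and the planned continuation trial. The article removes from randomisation the one group of partial refusers who could be randomised without overriding their refusal, does not say which arm they enter, and describes an analysis by group membership that would pool them with randomised women.

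For an assumed 10–30% of 75 declining only placebo, randomising them would lower the standard error of the randomised diet contrast by about 7–22%. At 2% the gain is 1.5%, which is negligible. The illustrative shift from pooling (0.07–0.21 SD at a 20% share) rests on assumed splits and an assumed prognostic difference, so it shows only what is possible.

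A reader might infer that staff or the women themselves choose between Gutopia and Gutboost. The text does not support that: it refers to preferences or needs and to screening responses, and is silent on who decides. What can be said is that no chance mechanism is described for these women.

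**What to change.** 1. In Trial design and setting, state that women who accept fish oil and probiotic but decline placebo are randomised 1:1 between Gutopia and Gutboost, from a separate list within the existing treated and untreated strata.
2. Keep assignment for women who decline probiotics or all products.
3. In Statistical analysis, stratify Gutopia versus Gutboost by willingness to take placebo, exclude placebo-decliners from the blinded Gutboost versus Gutless comparison, and analyse any assigned women separately from randomised women.
4. In the process outcomes, report placebo-decliners separately from fully randomised women, so that acceptance of full randomisation remains visible.

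**Cost:** one extra randomisation list and a few sentences; no more women or visits. Some Gutboost women will know that they receive the active probiotic and will contribute only to the diet contrast. Gutboost versus Gutless keeps the same fully randomised women as now (for example 20 per arm at f = 20%). If the sponsor prefers not to change allocation, naming the arm that placebo-decliners enter and analysing them apart from randomised women would remove the bias, but not recover the lost precision.
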